**Figure 1 figure1:**
[figure not shown]
Process flowchart.

### Technology

Comestai is a mobile app that leverages a combination of signal processing and artificial intelligence (AI) technologies, along with a proprietary mathematical backend server, to analyze the skin of the upper cheek region through a smartphone’s front camera (iOS or Android).

The Comestai app captures video images using signal processing AI technologies and analyzes the data using photoplethysmography techniques (Figure 2) [9,14-16]. This approach provides real-time measurements of physiological parameters, including SpO_2_, HR, PR, and RR, and biochemical parameters Hb, HbA_1c_, and total cholesterol. Unlike other apps, the app uses a novel technology that extracts ambient light RGB signals from face videos in real time, eliminating the need for cloud servers or an internet connection.

**Figure 2 figure2:**
[figure not shown]
Remote photoplethysmography from facial videos. RGB: red-green-blue.

### Equipment for Data Collection

For vital signs data collection using the Comestai app, the study staff will use the following mobile phones for remote photoplethysmography “by face” measurements:

Face—iPhone 13 Pro (10 bit) and Samsung Galaxy S21 UltraA total of 2 additional phones will be used remotely—Android phone (recorder remote for initiating measurements from a distance) and iPhone (Masimo app for collecting data from the Masimo finger sensor).Other necessary equipment includes phone stands (2 per measurement room).

In addition to the equipment for vital signs data collection using the Comestai app, reference devices will be used to measure the participant’s vital signs for comparative purposes.

#### Vital Sign Data Collection Using the Comestai App and Reference Devices

The study personnel will gather vital signs data in a designated room equipped with the following amenities: a table, a chair with a headrest and arm support, a white wall for participants to sit against, stable Wi-Fi, power sockets, and adequate lighting (if the room lacks sufficient illumination, one Theralite lamp per room will be necessary).

Vital signs data will be gathered using the Comestai app through the “by face” method and with the reference devices detailed in Table 1.

**Table 1 table1:** Reference devices for measuring vital signs.

Device	Saturation of oxygen	Pulse rate	Respiratory rate	Blood pressure
Withings BPM Connect				✓
Masimo mightySat Rx	✓	✓	✓	
Polar Verity Sense		✓		

Specifically, as reported in Figure 3, the measurement procedure flow will be as follows: first, The participant should sit for 2 minutes for stabilization with references connected. Second, baseline distance will be set at approximately 25 cm (closest as possible). Third, we will measure BP twice (if systolic ±10 and/or diastolic ±5, we will make a third measurement), waiting 1 minute in between the 2. Fourth, we will make 1 recording with each device. Fifth, we will measure BP twice (if systolic ±10 and/or diastolic ±5 make a third measurement).

**Figure 3 figure3:**
[figure not shown]
Measurement procedure flow.

The “by face” method for remote photoplethysmography vital signs data collection involves recording participants’ faces using the front camera of mobile devices (iOS and Android) for approximately 1.5 minutes.

During “by face” data collection, participants will be seated comfortably, facing a screen at approximately 25 cm, with their faces fully visible (without wearing masks, hats, or any facial accessories). Participants are required to maintain stable breathing and minimal movement and to gaze directly at the camera throughout the data collection process.

Simultaneously, vital signs data (SpO_2_, RR, BP, and PR) will be continuously collected for about 1.5 minutes using the reference devices alongside data collected via the Comestai app.

BP measurements will be taken using the reference devices before and immediately after data collection with the Comestai app.

### Data Collection and Management

Data from the investigational device will be collected by trained staff members. Vital signs data obtained using the app and reference data will be stored on a secured cloud. The app will be activated only when the cell phone is offline, ensuring that no information is stored in the Comestai cloud. Consequently, the company will not have access to any data collected during the tests.

In addition, the app will be deleted after use to prevent any data from being uploaded into the system. Data collected using the reference devices will be stored without any identifiable participant information and will only be identifiable using the participant identification number provided during screening.

The raw data of participants’ vital signs will be locked, encrypted, and accessible only to the study center team. Raw data can be processed only after unlocking the files to calculate the final measured results.

The coordinator center (Buzzi Children’s Hospital) will be responsible for securely storing the data in a locked and secured location. The Endocrinology Unit of ASST-Fatebenefratelli-Sacco and Buzzi Children’s Hospital will handle data entry and ensure data quality.

This study will be conducted in compliance with the Good Clinical Practice guidelines, including the archiving of essential documents.

No medical decisions will be made based on the data obtained from the Comestai app, reference devices, or blood sample results.

### Clinical Data Cleaning and Validation

Clinical data for the study will be meticulously organized, easily accessible, and thoroughly cleaned both throughout and after the study concludes (post data lock). Activities in clinical data management encompass data collection and entry, tracking electronic case report form (eCRF) usage, database design, data validation, and database locking.

As previously outlined, the eCRF will serve as the primary tool for capturing clinical data. The data fields within the eCRF are clearly defined and maintain consistency throughout. The eCRF is designed to be succinct, intuitive, and user-friendly.

Database edit checks will be conducted to identify discrepancies in the data, which could stem from inconsistent entries, missing data points, range discrepancies, or deviations from the study protocol. Any incomplete discrepancies will be addressed by site investigators. Continuous quality control measures for data processing will be implemented at regular intervals throughout the study duration.

### Criteria for Data Collection and Study Interruption

Temporal interruption of vital signs data collection using the app may occur in the following cases:

Technical issues with the investigational and/or reference devicesThe study may be interrupted for the following reasons:Breach of participant confidentiality.Decision by the principal investigator or institutional ethics committee.The investigators may also decide to terminate the study early if sufficient data has been collected for algorithm improvement.

### Statistical Analysis

Numerical variables will be presented as minimum and maximum values, means, SDs, medians, and quartiles. Categorical variables will be presented as absolute and relative frequencies.

The accuracy of the app measurements compared to the reference devices and standard tests will be assessed for all parameters. CIs will be calculated using the bootstrap method. Participants with abnormal adverse events (defined as 3 SDs or more above the mean) and those with invalid reference device values will be excluded from the analysis.

In order to provide a more comprehensive view of the model’s performance, the proposed approach’s effectiveness was evaluated using various quality criteria, including the mean error, SD, mean absolute error, root mean square error, and mean absolute percentage error. The correlation between measurements obtained using the app and those from reference devices and standard tests will be evaluated using the Pearson correlation coefficient. The agreement between the 2 sets of measurements (app vs reference devices/standard tests) will be represented using Bland-Altman plots. Sensitivity, specificity, positive predictive value, negative predictive value, accuracy, and likelihood ratios will be calculated to determine the ability of the new app to accurately measure vital signs.

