**Methods:**

A total of 3000 participants will be consecutively enrolled to achieve the objectives of this study. In all patients, personal data, medical condition, and treatment overview will be recorded. The “by face” method for remote photoplethysmography vital sign data collection involves recording participants’ faces using the front camera of a mobile device (iOS or Android) for approximately 1.5 minutes. Simultaneously, vital signs will be continuously collected for about 1.5 minutes using the reference devices alongside data collected via the Comestai app; biochemical results will also be recorded. The accuracy of the app measurements compared to the reference devices and standard tests will be assessed for all parameters. CIs will be calculated using the bootstrap method. The proposed approach’s effectiveness will be evaluated using various quality criteria, including the mean error, SD, mean absolute error, root mean square error, and mean absolute percentage error. The correlation between measurements obtained using the app and reference devices and standard tests will be evaluated using the Pearson correlation coefficient. Agreement between pairs of measurements (app vs reference devices and standard tests) will be represented using Bland-Altman plots. Sensitivity, specificity, positive predictive value, negative predictive value, accuracy, and likelihood ratios will be calculated to determine the ability of the new app to accurately measure vital signs.

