### Eligibility Criteria

Participants eligible for inclusion in the study must meet the criteria in Textbox 1.

In addition to the above criteria, 70% of the target population should include adult participants meeting at least one of the conditions in Textbox 2. Family history of diabetes or hypertension will also be investigated.

The procedures and evaluations in Textbox 3 will be performed during screening to enroll eligible participants.

Characterizing aspects will be noted, such as scars, piercings, beards, glasses, or the use of facial products, sunscreen cream, or nail polish. Furthermore, current pregnancy will be reported.

The flowchart of the process is schematized in Figure 1.

Inclusion and exclusion criteria.

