**Exclusion criteria**
Participants will be excluded if they meet any of the following conditions:Compromised circulation, injury, or physical abnormalities affecting fingers, hands, ears, forehead/skull, or other regions of interest essential for study testing.The presence of tattoos in the optical path hinders the assessment of necessary regions of interest.Severe allergies to standard adhesives, latex, or other materials used in medical sensors for measuring vital signs.Medical conditions that, in the investigator’s opinion, prevent the conduct of study assessments.Considered unfit for participation by the investigator.

Additional inclusion criteria.Prediabetes or diabetes with glycated hemoglobin (HbA_1c_) levels between 5.7% and 13%:30% of participants with HbA_1c_ 5.7%-6.4%.30% of participants with HbA_1c_ >6.4%.Hypertension with systolic measurements exceeding 130 mm Hg:40% of participants with systolic blood pressure >130 mm Hg.20% of participants with systolic blood pressure >160 mm Hg.Total cholesterol:40% of participants with levels >200 mg/dL and/or low-density lipoprotein cholesterol >130 mg/dL.Atrial fibrillation (~1% prevalence).Smokers, constituting approximately 20%-30% of the study cohort.

Procedures and evaluations.Obtain participant consent and, if agreed, additional consent for a blood sample.Review eligibility: assess eligibility as described in the inclusion and exclusion criteria.Record the participants’ medical and medication history: each medical problem encountered is classified into the sector of the body involved and for each of these, the starting date and the drugs used for treatment are indicated.Record participant demographics, including date of birth, age, smoking, and alcohol drinking habits.Record body characteristics including height, weight (BMI will be calculated as a person’s weight in kilograms divided by the square of height in meters), and skin tone using the Fitzpatrick scaleInterview the patient about his feelings in the last 2 weeks and if he has suffered from problems such as anxiety, nervousness, lack of control, loss of interest in doing things, or depression.

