### Sample Size Estimation

Considering the average values of pressure/saturation/HR among a general population with a sample of 3000 participants, there will be a power exceeding 95% for all evaluated parameters in a 2-sided test with a *P* value of .05 if the discrepancy between the 2 measurement methods is as reported in Table 2.

**Table 2 table2:** Expected error level of the measurements.

Vital	Range	Unit of measurement	Error level
Pulse rate	50-180	BPM^a^	RMSE^b^ ≤3
Respiratory rate	8-30	BrPM^c^	RMSE ≤3
Blood pressure systolic	80-180	mm Hg	MAE^d^ ≤15
Blood pressure diastolic	50-120	mm Hg	MAE ≤10

^a^BPM: beats per minute.

^b^RMSE: root mean square error.

^c^BrPM: breaths per minute.

^d^MAE: mean absolute error.

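### The bootstrap is the only confidence-interval method stated; for sensitivity and LR- it collapses to zero width when every one of a few abnormal cases is detected

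*Protocol article*

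**What the plan says.** The Statistical Analysis section of the protocol article states one interval method: "CIs will be calculated using the bootstrap method". It gives no exception, no bootstrap variant, no resampling unit and no alternative. Later in the same section: "Sensitivity, specificity, positive predictive value, negative predictive value, accuracy, and likelihood ratios will be calculated to determine the ability of the new app" to measure vital signs accurately. The Methods paragraph of the abstract has the same two elements. No cut-off for an abnormal value is given, nor an expected number of abnormal participants or an expected sensitivity.

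The planned sample is 3000. Under Eligibility Criteria, "70% of the target population should include adult participants meeting at least one of the conditions in Textbox 2". Textbox 2 then sets abnormal-value shares for HbA1c, systolic pressure (for example "40% of participants with systolic blood pressure >130 mm Hg", and half that share above 160 mm Hg) and cholesterol. It sets none for SpO2, pulse rate, respiratory rate or diastolic pressure.

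**The concern.** A nonparametric bootstrap learns about sampling error only from variation in the sample. If all abnormal participants are detected, there is no variation to resample: sensitivity is 100% in every resample and the interval runs from 100% to 100%. If none is detected, it runs from 0% to 0%. With no missed case, LR- = (1 - sensitivity)/specificity is 0 in every resample, so its interval is 0 to 0.

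This needs few abnormal cases, and the design makes that plausible for the vital signs without a quota. Participants are outpatients aged 16 to 65. They sit for two minutes before measurement and are asked to keep still and breathe steadily. That favours normal resting values.

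At stake is how the result is read. The Discussion looks toward use in screening, where the main question is how many abnormal cases the app might miss. The stated method would print its most certain-looking interval where the evidence is thinnest.

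**Working it through.** **The plan's own figures.** The documents give no interval width, coverage or abnormal count to reproduce. The one related figure is the power claim under Sample Size Estimation ("there will be a power exceeding 95% for all evaluated parameters in a 2-sided test"). No standard deviation or mean difference is given, so it cannot be rebuilt. It concerns the error measures and does not bear on this point.

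**Inputs from the documents.** N = 3000. The quota shares may refer to all 3000 or to the enriched 70%, which is 0.70 × 3000 = 2100. Ranges of abnormal cases:
- Systolic pressure above 130 mm Hg: 0.40 × 2100 = 840 to 0.40 × 3000 = 1200.
- Systolic pressure above 160 mm Hg: 0.20 × 2100 = 420 to 0.20 × 3000 = 600.
- HbA1c above 6.4%: 0.30 × 2100 = 630 to 0.30 × 3000 = 900.
- Cholesterol: 840 to 1200.

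The HbA1c and cholesterol counts are before any loss from optional consent to blood results.

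**Assumed inputs.** The number of abnormal cases n, the true sensitivity p, the percentile form of the bootstrap and a nominal level of 95%.

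**Formulas.** The number detected is x ~ Binomial(n, p). Given x, the resampled sensitivity follows Binomial(n, x/n)/n, and the limits are its 2.5% and 97.5% quantiles. Coverage is the sum of P(x) over those x whose interval contains p. The chance that all are detected, and hence of a 100%-100% interval, is p^n, so coverage cannot exceed 1 - p^n.

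**One case in full: n = 20, p = 0.95.**
- x = 20: probability 0.95^20 = 0.3585; the interval is 100%-100% and misses 0.95.
- x = 19, 18, 17, 16: probabilities 0.3774, 0.1887, 0.0596, 0.0133; intervals 17-20, 15-20, 14-20 and 12-19 out of 20. All contain 19/20 = 0.95.
- x = 15: the interval is 11-18 out of 20, which misses 0.95. Smaller x also miss.
- Coverage = 0.3774 + 0.1887 + 0.0596 + 0.0133 = 0.639.

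**Other cases, same method.**

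| n | p | P(100%-100%) | Bootstrap | Wilson | Clopper-Pearson |
|---|---|---|---|---|---|
| 20 | 0.95 | 35.9% | 63.9% | 92.5% | 98.4% |
| 30 | 0.95 | 21.5% | 78.2% | 93.9% | 98.4% |
| 20 | 0.90 | 12.2% | 87.6% | 95.7% | 98.9% |
| 30 | 0.90 | 4.2% | 95.0% | 97.4% | 99.2% |
| 50 | 0.95 | 7.7% | 91.1% | 96.2% | 98.8% |
| 100 | 0.95 | 0.6% | 95.9% | 96.6% | 98.3% |
| 100 | 0.98 | 13.3% | 86.6% | 94.9% | 98.5% |

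**What would be printed.** With 20 of 20 detected, the bootstrap lower limit is 100%. Clopper-Pearson gives 0.025^(1/20) = 83.2%, and Wilson gives 20/(20 + 1.96²) = 83.9%.

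**Quota-enriched endpoints.** For 420 to 1200 cases and p from 0.80 to 0.98, bootstrap coverage is about 91% to 96%, and the chance of a 100%-100% interval is at most 0.02%.

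**Likelihood ratios.** These were simulated with N = 3000, p = 0.95 and assumed specificity 0.90. Coverage for LR- is 39%, 63% and 77% at n = 10, 20 and 30. For LR+ it is 89%, 92% and 93%, with no collapse.

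**The case against.** The strongest reply has three parts.

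First, the bootstrap sentence stands next to the one on measurement accuracy and before the error metrics. The diagnostic indices come at the end of the section and are only to be calculated, with no interval mentioned beside them. The article is also condensed, and handling of zero misses is often left to a statistical analysis plan. A narrower reading is therefore possible. But the sentence has no restriction and no other method is named, so an analysis plan that follows it literally would inherit the problem.

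Second, no count, cut-off or sensitivity is documented, and the lack of a quota does not prove rarity. That stands. Diastolic pressure may be partly enriched through the systolic quota. Modest changes in the assumptions also remove most of the loss: coverage is 95.0% with 30 cases at sensitivity 0.90.

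Third, these indices are only one way the app is judged. Mean error, SD, MAE, RMSE and MAPE come first, and the sample size is tied to RMSE and MAE limits. That also stands, and the bootstrap suits those measures.

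Two stronger inferences are tempting and fail. A reader might take atrial fibrillation, at about 1% of the cohort, as the documented rare case. It describes who is enrolled and is not listed as an app measurement, so no sensitivity for it is planned. A reader might also expect LR+ to become infinite. That needs resamples with no false positive, which have probability about e^-k when k false positives are observed. This exceeds 2.5% only for k of 3 or fewer (e^-3 = 5.0%, e^-4 = 1.8%). Among nearly 3000 unaffected participants, that means specificity of about 99.9%.

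**Conclusion.** The point holds in a limited form. The only stated interval method, read as written, gives a zero-width interval for sensitivity when all or none of the abnormal cases are detected, and a 0-to-0 interval for LR- when none are missed. That is arithmetic and needs no assumption beyond a nonparametric bootstrap.

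How often it would happen, and how much coverage is lost, depends on assumed counts and sensitivity. Coverage ranges from 64% to 96% over the four cases given in the summary. A reader might infer that the plan's intervals have coverage near 65% in general. The documents do not support that: the figure belongs to about 20 cases at sensitivity 0.95. The exposure is confined to endpoints without a quota, chiefly SpO2, pulse rate and respiratory rate. Systolic pressure, HbA1c and cholesterol are essentially unaffected. This is a modest, low-cost correction and does not undermine the main error analysis.

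**What to change.** Replace the single sentence on intervals with a rule by type of measure:
- Bootstrap intervals for mean error, MAE, RMSE, MAPE and correlation.
- Wilson or Clopper-Pearson intervals for sensitivity, specificity, predictive values and accuracy.
- A score-type interval for likelihood ratios. The uncorrected log method should not be used, because with no missed case LR- is 0, its logarithm is undefined and its variance contains 1/0.
- The number of abnormal participants printed beside each index.

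The cost is a sentence or two of analysis text and no new data. Some intervals become wider, which reflects the evidence, and Clopper-Pearson is somewhat conservative (98-99% coverage in the four summary cases). Results for the quota-enriched endpoints barely change.

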### Known Potential Risks and Benefits of the Investigational Device

#### Potential Risks

No adverse device effects are expected from the Comestai app, and there are no contraindications for its use in the study population. However, unforeseeable risks related to the data collection process may arise.

One such risk is the potential breach of participant confidentiality due to improper data storage. In order to mitigate this, vital signs data will be securely stored on Comestai’s cloud. Videos of faces obtained using the “by face” method will be anonymized, and recognized only by the participant identification number assigned during screening. The raw vital signs data will be locked, encrypted, and accessible solely by the study center team. Processing of this data will only occur once the files are unlocked.

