Although the protocol included participants with diseases such as hypertension, prediabetes and diabetes, dyslipidemia, and atrial fibrillation to assess the tool’s accuracy even in the presence of pathological values, conducting the study in a controlled setting can be considered a limitation. Its application in real-life scenarios may present challenges that were not accounted for.

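### The 3-SD exclusion names no variable and removes participants whose reference value is valid, so it may discard large app errors or high readings the study needs

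*Protocol article*

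**What the plan says.** The Statistical Analysis section gives two grounds for exclusion in one sentence: "Participants with abnormal adverse events (defined as 3 SDs or more above the mean) and those with invalid reference device values will be excluded". The first ground is numerical and upper-sided, and it acts on the whole participant. The mean and SD are not tied to any variable: app error, app reading and reference reading are all possible. No analysis that keeps these participants is mentioned.

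The same section then lists the accuracy measures, "including the mean error, SD, mean absolute error, root mean square error, and mean absolute percentage error", together with Bland-Altman plots. Table 2, under Sample Size Estimation, gives expected error levels: RMSE of at most 3 for pulse and respiratory rate, and MAE of at most 15 and 10 mm Hg for systolic and diastolic pressure.

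The additional inclusion criteria (Textbox 2) set quotas for abnormal values, such as "20% of participants with systolic blood pressure >160 mm Hg" and HbA1c up to 13%. Strengths and Limitations explains that such participants are included to assess "accuracy even in the presence of pathological values".

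**The concern.** An adverse event has no mean or SD, so the rule cannot be applied as worded. It has to act on some measured quantity, and each workable choice removes data that the accuracy estimate needs. A cut on app-reference error deletes the largest errors before the error is summarised. A cut on readings can delete the extreme values that the quotas were written to supply.

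At stake is whether the published RMSE, MAE and limits of agreement describe the app in everyone who could be measured, or only in those left after an outcome-dependent filter. Gross misreads matter most for the self-monitoring use the article has in view, and they are what an error-based cut removes first. Because the variable is unnamed, it could also be chosen after the data are seen.

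**Working it through.** **No figure of the plan to reproduce.** The only related figure is the power above 95% at N = 3000. The article gives no null hypothesis and no SD, so it can be neither reproduced nor refuted, and this point does not rest on it. For scale, a paired comparison with 95% power detects a bias of (1.960 + 1.645)/√3000 = 0.066 SD. Losing a few dozen participants does not threaten power. The issue is bias.

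**Cut on absolute error.** Let |e| have mean m and SD s. Every removed value satisfies |e| ≥ m + 3s. This exceeds m, which is the MAE. Its square exceeds m² + s², which is the mean squared error. MAE and RMSE therefore always fall, whatever the distribution.

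**Upper cut on signed error.** Let the error have mean b·s and SD s.

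- Removed points lie at or above (b + 3)s, and the mean squared error is (b² + 1)s².
- RMSE is certain to fall when (b + 3)² > b² + 1, that is 6b + 8 > 0, or b > -1.33.
- Below that the guarantee ends. For normal errors the trimmed mean squared error is s²[b² + 1 - k(3 + 2b)], with k = φ(3)/Φ(3) = 0.00444, so the direction reverses at b = -1.5.
- At b = -2 and s = 1, RMSE goes from 2.236 to 2.237, a very slight rise.
- The mean error always shifts downward.

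**Size for pulse rate, Table 2 expected RMSE 3.** The article gives no error distribution, so both shapes below are assumptions.

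| Assumed errors | Analysis | Dropped of 3000 | RMSE | Mean error |
|---|---|---|---|---|
| Normal, SD 3 | all kept | 0 | 3.00 | 0 |
| | signed, above mean + 3 SD | 4 | 2.98 | -0.01 |
| | absolute, above mean + 3 SD | 27 | 2.89 | 0 |
| 95% SD 2.5, 5% SD 10 | all kept | 0 | 3.31 | 0 |
| | signed, above mean + 3 SD | 24 | 3.00 | -0.12 |
| | absolute, above mean + 3 SD | 52 | 2.63 | 0 |

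Two entries can be checked by hand. The untrimmed mixture is √(0.95 × 2.5² + 0.05 × 10²) = √10.94 = 3.31. The signed cut with normal errors is 3 × √(1 - 3 × 0.00444) = 2.98.

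MAE moves less than RMSE. In the mixture it falls from 2.29 to 2.19 (signed) or 2.07 (absolute), about 5% and 10%. Over a wider set of assumed shapes (normal, t, and mixtures with 2% or 5% failures of varying size and direction), RMSE falls by 0.7% to 35% and MAE by 0.4% to 20%.

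**Cut on readings.** Values were built from the Textbox 2 quotas, again with assumed shapes.

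- HbA1c with a right-skewed tail (exponential above 6.4%, mean excess 1 to 2 points, capped at 13%): the cut falls at about 8.8% to 11.3%, inside the recruited range, and drops about 49 to 83 of 3000.
- HbA1c with a flat tail to 13%: mean 6.83, SD 2.19, cut about 13.4%, nobody dropped.
- Systolic pressure built on the quotas: the cut falls at 190 to 215 mm Hg, so nobody within the 80-180 range of Table 2 is dropped. About 50 of 3000 go if the tail runs to 220.

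**The case against.** The strongest defence is that the effect is conditional and may be small. With well-behaved normal errors, the one-sided cut that the text literally describes removes about 4 of 3000 participants and moves RMSE by less than 1%. If the app reads strongly low, the cut can even raise RMSE slightly. That stands, and it limits what can be said about size. It does not justify the rule, whose effect is largest when the app fails grossly.

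Several stronger readings are tempting, but the documents do not support them:

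- **Accuracy is necessarily overstated.** This is assured for an absolute-error cut and likely for a signed one. On the readings interpretation it also needs larger app error at extreme values, which the article does not state.
- **A failing app would be passed.** Table 2 lists expected error levels as sample-size assumptions, and the Statistical Analysis section sets no success test against them. In the 5% gross-error example, the one-sided signed cut lands on 3.00, at the level and not clearly below it. Only the absolute version goes well under.
- **The quotas recruit high pulse rates and all high pressures are lost.** Textbox 2 has no pulse-rate criterion. Atrial fibrillation, at about 1%, is a rhythm diagnosis. Systolic values within 80-180 are untouched when the distribution is built on the quotas.
- **The Potential Risks section rules out adverse events as the subject.** It says "No adverse device effects are expected from the Comestai app", which concerns device effects, and it allows for unforeseeable risks of data collection. The sound argument is only that an adverse event has no mean or SD.

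It may also be said that exclusion details belong in the full protocol or SAP. That would answer an omission, but here the article states the rule. The edit checks under Clinical Data Cleaning and Validation already deal with range and entry discrepancies, and nothing elsewhere restores the excluded participants.

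**Conclusion.** The point holds in conditional form. The rule is undefined, upper-sided, and additional to the invalid-reference ground, so following it removes valid pairs from the main accuracy analysis.

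On the error interpretation it selects on the outcome, and normally in the app's favour. The exception is a signed cut when mean bias is below about -1.33 SD. On the readings interpretation it can conflict with the stated purpose of recruiting pathological values, most plausibly for a skewed HbA1c tail, and it overstates accuracy only if error grows at those extremes.

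The size is unknown. Under the two tabulated error shapes, the fall in RMSE runs from under 1% (normal errors, signed cut) to about 21% (5% gross errors, absolute cut). These figures rest on assumed distributions and illustrate the mechanism. They do not predict this trial's result.

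**What to change.** Remove the 3-SD exclusion from the main analysis and analyse every participant with a valid reference value. Exclude only for invalidity of the reference device, judged without sight of the app value. The detailed criteria can sit in the full protocol or SAP. If a 3-SD-trimmed result is wanted, show it only as a labelled sensitivity analysis that names the trimmed variable and reports the number dropped. Replace the reference to adverse events in that sentence, since the cut cannot apply to them.

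The cost is one paragraph of text. No additional data are needed. The reported error figures may be slightly less favourable.
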